## Subjects and methods

### Study design

This study was registered on www.chictr.org.cn in November 2024 (ID: ChiCTR2400092245) and approved by the Ethics Committee of Beijing Luhe Hospital, Capital Medical University, China (2024-LHKY-092-03). All study participants were fully informed about the research process, risks, and benefits, and voluntarily agreed to participate by signing an informed consent form. The study protocol and informed consent form were approved by the Ethics Committee.

A total of 40 participants will be randomly assigned to either the observation group (RIC group) or the control group (sham RIC group), with 20 participants in each group. All participants with AD included in the study will continue receiving standard pharmacotherapy in accordance with established clinical practice guidelines. Each group will begin RIC or sham treatment, administered once daily for 45 min per session over a period of 3 months.

Specifically, our study has established a Data and Safety Monitoring Board (DSMB) composed of independent experts to ensure rigorous oversight of participant safety, data integrity, and scientific validity throughout the trial. The DSMB is responsible for regularly reviewing accumulated safety data, monitoring adverse events, and making recommendations regarding study continuation or modification as needed to protect participant welfare.

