### Statistical analysis

Data will be obtained from all patients who complete the study protocols and follow-ups and will be analyzed using the per-protocol (PP) approach. Statistical analysis will be performed using SPSS version 20 (SPSS Inc., Chicago, IL, United States), with a significance level of *p* < 0.05. Demographics and clinical characteristics will be analyzed using descriptive statistics. Continuous and categorical data will be reported as mean values, standard deviations, number values, and percentages. Continuous variables following a normal distribution will be compared using the independent samples *t*-test, ANOVA, or rank-sum test, while categorical variables will be compared using the chi-square test.

In our RIC trial in mild Alzheimer’s dementia (*n* = 40), we implemented two strategies appropriate for small-sample longitudinal data. First, single random forest imputation was applied to address missing cognitive scores (e.g., MoCA/MMSE) by using predictors such as baseline Aβ42/Aβ40 ratio and RIC adherence preserve variable interaction structure. Second, Generalized Estimating Equations (GEE) will be used to model outcome trajectories under the assumption of missing at random (MAR), thereby accommodating incomplete data without imputation. Attrition is minimal (7% MoCA loss at 12 months) and APOE subgroup analyses show no evidence of differential dropout. This approach balances methodological rigor with feasibility and aligns with CONSORT recommendations for early-phase trials with limited resources.

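### The Statistical analysis section gives the cognitive scales three incompatible analysis bases (per-protocol completers, imputed scores, GEE on incomplete data) at one p < 0.05, with none named as deciding

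*Protocol article*

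**What the plan says.** All of this stands in the Statistical analysis section of the protocol article.

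- **Patient set.** "Data will be obtained from all patients who complete the study protocols and follow-ups and will be analyzed using the per-protocol (PP) approach".
- **Threshold.** The analysis is run "with a significance level of *p* < 0.05". No other level is given, and no test is exempted.
- **Tests.** Continuous variables described as normally distributed "will be compared using the independent samples *t*-test, ANOVA, or rank-sum test". No test is named for continuous variables that are not normal.
- **Imputation.** "First, single random forest imputation was applied to address missing cognitive scores", with the baseline amyloid ratio and RIC adherence among the predictors.
- **Longitudinal model.** GEE will model outcome trajectories under MAR, "thereby accommodating incomplete data without imputation". Which contrast is tested (group by time, average group effect, or the difference at a visit) is not stated.

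Imputation and GEE are introduced as two strategies side by side. Neither is called main or supportive, and neither is related to the per-protocol sentence. The same section puts MoCA loss at 12 months at 7%.

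**The concern.** The three statements define different data sets for the same scales. If completing the protocol and all follow-up is the entry condition, patients with missing visits are already out, so imputation and an incomplete-data model have almost nothing to act on. If imputation or GEE defines the analysis, patients with missing visits are in, and the per-protocol sentence does not describe it.

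The targets differ too: a mean difference among completers, a mean difference in a filled-in data set, and a difference in trajectory. With 20 patients per arm, a few patients moving in or out can change a borderline result, and the plan as written would support citing whichever version was significant. Reducing the number of scales or visits would not remove the conflict between patient sets.

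The choice of set may also interact with treatment. The cuffs inflate to 200 mmHg in one arm and 60 mmHg in the other (Interventions), and patients who cannot tolerate the procedure are suspended (Outcomes for safety). Completion could therefore differ by arm. That possibility is not quantified below.

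**Working it through.** **Step 1: the sentences side by side.** Applied to 40 randomised patients with the section's own 7% loss, 0.07 × 40 = 2.8, so about three patients lack a 12-month MoCA. The per-protocol rule drops them, together with anyone else who did not complete the protocol. Imputation keeps them with a predicted score. GEE keeps them with the visits they have. These are three data sets, and the document does not rank them.

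**Step 2: inputs for the error rate.**
- From the protocol: 20 per arm (Study design); visits at baseline, 3, 6 and 12 months (Neuropsychological assessments); threshold 0.05 and 7% loss (Statistical analysis).
- Assumed, because the protocol gives no figure: two-sided tests; within-patient correlation 0.6 or 0.8; 20% loss as an alternative to 7%; extra per-protocol exclusions of 0% or 10%; normal, rounded MMSE-like or skewed outcomes; non-completion at random.
- Stand-in: regression prediction in place of random forest. GEE used an exchangeable working correlation and a robust Wald test.

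The simulation assumed no treatment effect and ran 3,000 trials in each of 7 scenarios. The Monte Carlo standard error is √(0.05 × 0.95 / 3000) = 0.4 points near 5% and √(0.13 × 0.87 / 3000) = 0.6 points near 13%.

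**Step 3: the plan's own figure.** The per-protocol t-test alone gave 4.9–5.5%, which agrees with the nominal 5%.

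**Step 4: chance that at least one listed analysis of one scale gives p < 0.05** (t-tests and rank-sum at 12 months; range over the 7 scenarios).

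| Analyses that may be cited | False-positive rate |
|---|---|
| t-test or ANOVA, per-protocol | 4.9–5.5% |
| t-test or rank-sum, per-protocol | 5.6–6.7% |
| t-test or rank-sum, per-protocol and imputed | 7.2–8.6% |
| Per-protocol t-test, imputed t-test, GEE at the same visit | 6.4–8.7% |
| Both tests on both sets, GEE at the same visit | 8.2–9.5% |
| Both tests on both sets, GEE average group effect | 10.0–11.4% |
| Per-protocol t-test, imputed t-test, GEE group-by-time | 11.0–12.9% |
| Both tests on both sets, GEE group-by-time | 12.3–13.9% |

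For scale, three independent tests would give 1 − 0.95³ = 14.3%.

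**Step 5: what drives the figure.** ANOVA adds nothing, since with two arms its p-value equals that of the t-test. Within scenarios, rank-sum adds 0.6 to 1.7 points to the t-test. The largest step comes from a trajectory contrast, which draws on other visits.

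**Step 6: GEE on its own.** With an uncorrected robust variance, GEE alone ran at 5.4–7.2%, so part of the excess in the GEE rows is its own small-sample size. It is not the whole explanation. A separate simulation (6,000 runs per scenario, correlations 0.5–0.8, normal data) replaced GEE by a per-person slope test of about the right size. It gave 9.7–10.3% for the completer t-test or the slope test, and 11.0–12.7% once rank-sum and the imputed t-test were added.

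**The case against.** Four points can fairly be made for the plan.

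**This is a condensed article.** Labels such as main and sensitivity, and the rule for choosing between t-test and rank-sum, commonly sit in a statistical analysis plan. That stands for the missing labels and for the choice of test. It does not rescue the patient sets: a later document can rank analyses, but it cannot make a completers-only rule agree with imputing and modelling patients who did not complete. An isolated missing score in a patient who attended every visit could still be imputed, but the section frames the problem as attrition and dropout.

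**Nothing says that any significant result counts as success.** This stands. The test list is generic and follows the descriptive statistics, and imputation is presented as a way of handling missing data. The rates above describe what the wording permits, not what the sponsor has announced.

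**A reader might infer that one scale at one visit carries 11–13%, about twice the stated level.** The documents do not support that. Rates of 11% and above with GEE group-by-time need a contrast across visits. This is a fair reading of modelling trajectories, but it is not stated, and it is not a single-visit comparison. Where GEE tests the same visit, the range is about 6–10%. Nor is the test list the heart of the matter, given its 1–2 points.

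**A reader might also infer that a cognitive p-value decides whether RIC moves to Phase II.** No section says so. Sample size estimation ties Phase II to safety and feasibility, and Outcomes for efficacy lists the scales as secondary. The Abstract and Discussion do give these scales primary status for efficacy, so their analysis matters, but not as a go/no-go rule.

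**Conclusion.** The point holds as an internal contradiction. The per-protocol, imputed and incomplete-data statements cannot all govern the cognitive scales, and with one threshold and no deciding analysis the plan does not say which result is the trial's result.

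The cost in false positives is conditional. It is about 6–10% for one scale if GEE tests the same visit and about 11–14% if it tests group by time, against 5%, provided any of the analyses may be cited. These figures rest on assumed correlations, dropout at random and a regression stand-in for the random forest. None comes from the protocol, and they do not count any effect of completion differing between arms. Since efficacy is preliminary in a Phase I trial, this should be corrected, but it does not undermine the safety aim.

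**What to change.** In the Statistical analysis section, replace the per-protocol sentence, as far as the cognitive and functional scales are concerned, with one deciding analysis:

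- one longitudinal model on all randomised participants with any follow-up data;
- the RIC–sham difference at one named visit as the contrast;
- if the model is GEE, a stated small-sample variance correction, because naming GEE without one would not by itself hold 5% at 40 patients.

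Label the per-protocol comparison, the imputed-data comparison and the overall trajectory test as sensitivity analyses without significance claims. Limit rank-sum to non-normal variables and drop ANOVA from the two-arm comparison, where it duplicates the t-test.

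With a single pre-named test the simulated rate returns to about 5% (per-protocol t-test 4.9–5.5%, imputed t-test 4.6–5.4%); the corrected GEE itself was not simulated. The change costs a few sentences and needs no new patients or data. The sponsor gives up the freedom to choose among analyses afterwards.

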### Sample size estimation

This is a Phase I trial measuring the safety and feasibility of RIC. Since no prior clinical studies have examined RIC in AD patients, there is no reference data available. Ganesh proposed that a cohort of 12 patients per group is sufficient to assess the safety of remote ischemic conditioning in patients with Vascular Cognitive Impairment (28). Tong’s Phase I clinical trial on the safety and efficacy of RIC in stroke patients suggested that 20 cases are sufficient to assess the feasibility of a pilot study (29). Based on studies addressing the safety and feasibility of RIC, this project targets 20 patients in each group, providing sufficient confidence to proceed to a subsequent Phase II study with a randomized sham control.

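### Missing cognitive scores: single imputation, a completers-only analysis and an unimputed GEE are all planned with no main analysis named, and a standard test on the singly imputed scores has either too small a standard error or a diluted effect

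*Protocol article*

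**What the plan says.** The Statistical analysis section of the protocol article treats missing cognitive data in three ways.

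- **Completers only.** It opens with: "Data will be obtained from all patients who complete the study protocols and follow-ups and will be analyzed using the per-protocol (PP) approach".
- **Single imputation.** It then says that "single random forest imputation was applied to address missing cognitive scores" and that this is done "by using predictors such as baseline Aβ42/Aβ40 ratio and RIC adherence". No multiple imputation, bootstrap or other variance correction is mentioned.
- **GEE.** The second of its two strategies for small longitudinal samples is a GEE under missing at random, "thereby accommodating incomplete data without imputation".

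Continuous variables are to be "compared using the independent samples *t*-test, ANOVA, or rank-sum test", "with a significance level of *p* < 0.05". The section does not say which of these tests uses the imputed scores, or which of the three approaches is the main one. The only figure for missing data is "Attrition is minimal (7% MoCA loss at 12 months".

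The status of the scales also varies. Outcomes for efficacy lists MMSE, MoCA, CDR and ADL as secondary outcomes, while the Abstract calls them primary efficacy endpoints.

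**The concern.** One filled-in value per missing score carries no imputation uncertainty. A random forest prediction is also an average over trees, so filled-in values vary less than real scores would. A t-test on the completed data counts them as observations.

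What follows depends on the imputation model. With arm among the predictors, each missing score is drawn towards its own arm's mean. The estimated difference is then unbiased, but its standard error is too small. Without arm, imputed values in both arms are drawn towards a common value and a true difference is diluted.

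The three approaches also conflict. Read strictly, a patient with no 12-month score has not completed follow-up and falls outside the per-protocol set, so there is little left to impute. The GEE uses that patient's earlier visits. The imputation supplies a 12-month value. These can give three different answers, and with no order fixed in advance the most favourable can be reported. Sample size estimation says that the trial should give confidence to proceed to Phase II, so the cognitive results are likely to be read as evidence.

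**Working it through.** **Inputs from the protocol article.** 20 per group (Sample size estimation: "this project targets 20 patients in each group"), significance level 0.05, and 7% MoCA loss at 12 months. The article gives no SD, effect size or power, so there is no sample-size figure to reproduce. As a count, 0.07 × 40 = 2.8. The nearest whole number is 3, and 3/40 = 7.5%.

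**Assumptions not in the article.** Two-sided test; t-test at 12 months on the completed data; scores missing completely at random; between-visit correlation 0.7 for type I error, and 0.5 and 0.7 for dilution; a 20% loss (8 of 40) as a less favourable case.

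**1. Upper case by formula, arm included.** Suppose that the other predictors carry no information, so each missing score is replaced by its arm mean. With n = 20 per arm and m observed, the completed arm's sum of squares is still (m − 1)s². The reported variance of the arm mean is therefore (m − 1)s²/[n(n − 1)], while the true variance is s²/m. Hence

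reported SE / true SE = √[m(m − 1) / (n(n − 1))].

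- 7% loss: m = 18.6; √(18.6 × 17.6 / 380) = 0.928. The critical value 2.024 (38 df) acts as 2.024 × 0.928 = 1.879. The two-sided tail of t with 35.2 df is 6.9%.
- 20% loss: m = 16; √(16 × 15 / 380) = 0.795. The critical value acts as 1.609, and the tail with 30 df is 11.8%.

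**2. Type I error by simulation under no effect** (mean reported SE divided by true SD in brackets). Linear rows use 20,000 runs. Random forest rows use 4,600 to 6,700 runs, with Monte Carlo error of about 0.3 to 0.4 points.

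| Imputation | Arm a predictor | Earlier scores predictors | 3 of 40 missing | 8 of 40 missing (assumed) |
|---|---|---|---|---|
| Random forest | no | yes | 5.0% (1.00) | not run |
| Random forest | yes | yes | 5.2% (0.98) | 5.9% (0.98) |
| Random forest | yes | no | 6.6% (0.95) | 8.8% (0.89) |
| Linear | no | no | 5.2% (0.99) | 5.0% (0.99) |
| Linear | no | yes | 5.0% (0.99) | 5.1% (0.99) |
| Linear | yes | yes | 5.8% (0.96) | 7.7% (0.90) |
| Linear | yes | no | 7.4% (0.92) | 12.1% (0.78) |

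Observed cases alone, in the same simulations, gave 4.8% to 5.4%. Multiple imputation was not simulated.

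**3. Dilution when arm is left out.** With uninformative predictors, imputed values have the same expectation in both arms. The completed-data difference is then (1 − f) times the true one, where f is the missing share. For f = 3/40 the loss is 7.5%; for f = 8/40 it is 20%. Simulations with linear imputation gave about 4% to 8% at 3 of 40 and about 9% to 21% at 8 of 40. If the 3- and 6-month scores are predictors, they carry much of the arm effect, and shrinkage fell to about 1% to 3% and 7% to 9%. With arm included there was no dilution (ratio 0.99 to 1.01).

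**The case against.** A reader might infer that false-positive rates are bound to exceed 5%, and that the cognitive p-values are both too small and biased towards zero. The document does not support that. The two harms need opposite imputation models and cannot both apply in full. The list of predictors is introduced by "such as": arm and earlier scores are neither named nor excluded, and the full model may properly be left to an analysis plan that is not shown. With a random forest, the method actually planned, type I error at the stated loss lies between 5.0% and 6.6%. The case with arm and earlier scores (5.2%) cannot be told apart from nominal. The linear figures overstate the random forest effect, and the 20% loss is hypothetical.

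The GEE works on unimputed data and is untouched by this mechanism. The trial is a Phase I safety and feasibility study, and no decision rule rests on a cognitive p-value.

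All of this stands, and it limits the size of the problem. It does not remove it. Single imputation is a method that the article itself chooses, not a detail that it leaves open. Either way of completing the predictor list leaves a defect, though a small one if earlier scores are used. The GEE does not settle the matter, because it is not named as the main analysis. Unweighted GEE is also not generally valid under the missing-at-random assumption that the article gives it. Nor is 7% a safe ceiling for a plan with daily station visits for 3 months and follow-up to 12 months.

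**Conclusion.** The point holds in a limited form. The firmest part needs no simulation: three incompatible treatments of missing cognitive scores are named and none is the main one.

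The single imputation adds a defect whose direction depends on an unstated choice. At the stated loss, type I error can exceed 5%, but only modestly: 5.0% to 6.6% with a random forest, up to about 7.4% with linear imputation including arm. If arm is left out there is no inflation, and a true effect shrinks by up to about 8%, less if earlier visits are predictors. At an assumed 20% loss, type I error is about 6% to 12% with arm, or shrinkage is about 9% to 21% without it.

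These sizes rest on the assumptions listed with the check, above all data missing completely at random and a t-test on the completed scores. They do not apply to the GEE. How much they matter also depends on whether the scales are secondary (Outcomes for efficacy) or primary efficacy endpoints (Abstract), which the article should reconcile.

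**What to change.** Drop single imputation. Name one main analysis of the cognitive scores, in all randomised patients with any follow-up. Replace the GEE with a likelihood-based mixed model for repeated measures containing arm, visit, arm-by-visit and baseline score. The article does not at present contain such a model. It needs no imputation and is valid under the missing-at-random assumption that the plan already states.

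As a sensitivity analysis, use multiple imputation with 20 or more sets combined by Rubin's rules. Its predictors should include arm, baseline and earlier scores on the same scale, and adherence. Label any completers-only analysis as supportive.

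The cost is a change of wording, a little programming and slightly wider confidence intervals. No extra patients or visits are needed.

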### Neuropsychological assessments

The Mini-Mental State Examination (MMSE), Montreal Cognitive Assessment (MOCA), and Clinical Dementia Rating (CDR) scales will be used to evaluate the cognitive function of patients with mild Alzheimer’s dementia. The Activities of Daily Living (ADL) scale will be used to assess their quality of life. The Hamilton Anxiety Rating Scale (HAMA) and the Hamilton Depression Rating Scale (HAMD-17) will be used to evaluate the mental and emotional status. These assessments will be conducted at baseline, 3 months, 6 months, and 12 months.

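### The protocol credits GEE with validity under MAR, which ordinary unweighted GEE does not generally have; the arm comparison can be biased if score-dependent dropout differs by arm

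*Protocol article*

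**What the plan says.** All of this is in the protocol article, under Statistical analysis, unless noted.

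- Longitudinal model: "Generalized Estimating Equations (GEE) will be used to model outcome trajectories under the assumption of missing at random (MAR"), and as a consequence "thereby accommodating incomplete data without imputation". No weighting and no working correlation are named.
- A second missing-data method beside it: "single random forest imputation was applied to address missing cognitive scores".
- Analysis set: "Data will be obtained from all patients who complete the study protocols and follow-ups and will be analyzed using the per-protocol (PP) approach".
- Dropout: "Attrition is minimal (7% MoCA loss at 12 months"), with no numerator, denominator or split by arm. The only evidence offered on the mechanism is "APOE subgroup analyses show no evidence of differential dropout".
- Design: 40 patients "with 20 participants in each group" (Study design). For the scales, "These assessments will be conducted at baseline, 3 months, 6 months, and 12 months" (Neuropsychological assessments).

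The Abstract calls MMSE, MoCA, CDR and ADL primary efficacy endpoints. Outcomes for efficacy lists them as secondary. GEE is the only longitudinal model named for them.

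**The concern.** MAR allows the chance of dropping out to depend on scores already observed. Unweighted GEE solves its estimating equations on the records that are present, so its validity does not in general extend to that case. The protocol therefore asserts a property of the named method rather than leaving a detail open, and a later analysis plan would inherit the wrong justification.

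What is at stake is the 12-month comparison on the cognitive and functional scales. Dropout linked to both score and arm is conceivable from the protocol itself. Patients attend daily for 3 months, cuff pressure differs between the arms (200 against 60 mmHg), intolerance of the procedure leads to suspension from the study, and Outcomes for safety says that cuff pressure may worsen the distress that comes with cognitive decline. The APOE check does not address dropout by arm or by earlier score.

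**Working it through.** **The plan's own figure.** The sample size rests on precedent, so there is no formula to reproduce. The one relevant number is the 7% loss: 0.07 × 40 = 2.8 patients. The nearest whole counts give 2/40 = 5.0% and 3/40 = 7.5%, so 7% cannot be reproduced exactly on 40 patients.

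**Inputs from the protocol.** 20 per arm; visits at 0, 3, 6 and 12 months; 7% loss at 12 months.

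**Assumptions not in the protocol.** SD 4 points at each visit; true correlation either exchangeable 0.7 or AR(1) with 0.85 between adjacent visits; dropout before month 12 depends on the observed 6-month score with a log-odds slope of 1.5 per SD; loss is equal in the two arms; true 12-month effect 0 or 2 points. Losses of 15% and 30% were added to show the range.

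**Formula for the independence working correlation.** With a separate mean for each arm and visit, the 12-month estimate is the mean of the patients still present. Its bias in one arm is

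bias = ρ × SD × m,

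where ρ is the correlation between months 6 and 12, and m is the mean standardised 6-month score among those who stay. Numerical integration of the logistic dropout model gives m = 0.088 at 7% loss, 0.175 at 15% and 0.327 at 30%. At 7% loss:

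- ρ = 0.7: 0.7 × 4 × 0.088 = 0.25 points
- ρ = 0.85: 0.85 × 4 × 0.088 = 0.30 points

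If low scorers leave one arm and high scorers leave the other, the two biases add: 0.49 to 0.60 points.

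**Large-sample simulation (2,000,000 patients), bias in points, independence working correlation.**

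| Loss | Arm difference, same mechanism in both arms | Arm difference, score-dependent in one arm only | Arm difference, opposite dependence |
|---|---|---|---|
| 7% | about 0 | 0.25–0.31 | 0.50–0.60 |
| 15% | about 0 | 0.47–0.59 | 0.97–1.19 |
| 30% | about 0 | 0.91–1.12 | 1.83–2.23 |

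With the same mechanism in both arms, each arm mean is still biased: by 0.25 to 0.30 points at 7% and by 0.9 to 1.1 at 30%.

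**Other working correlations.** A misspecified exchangeable structure gives at worst about 0.08 points at 7%, 0.14 at 15% and 0.26 at 30%. With the true correlation, which here is equivalent to a likelihood-based model, bias is at most 0.02 points, which is simulation noise. Under MCAR it is about zero throughout.

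**Scale.** The standard error of a 12-month difference is 4 × √(2/20) = 1.26 points, or 1.26/4 = 0.32 SD. The worst case at 7% is 0.60/4 = 0.15 SD, and 0.60/1.26 = 0.48 of a standard error. At 30% the worst case is 2.23/4 = 0.56 SD.

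**A second simulation** used 20 per arm, SD rising over time and score-dependent dropout in one arm only. At 4%/9% loss in the two arms it gave a bias of 0.12 baseline SD with independence and 0.03 with exchangeable working correlation, the same order of size.

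**The case against.** The strongest case against has four parts.

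- **A reader might infer that any dropout depending on earlier scores biases the comparison.** It does not. When the same mechanism acted in both arms, the difference was unbiased even at 30% loss. The protocol nowhere says that dropout differs by arm. This stands, and limits the claim to arm-differential dropout. A common mechanism still distorts the arm means, and the protocol says GEE is to model trajectories.
- **The working correlation is a detail that an article may leave to the full plan, and a correct one removes the bias.** This also stands: its absence is not the finding. The finding is the unqualified statement that GEE handles MAR data, when that depends on exactly this choice or on weighting.
- **Loss is only 7%.** At that loss the effect is small. A reader might infer from heavier-attrition scenarios that false positives are badly inflated. In the second simulation at 14%/21% loss the rate was 12.6% with independence but 6.1% with exchangeable working correlation. Complete data with an uncorrected sandwich z-test (an assumed test) already give 6.2%. Those losses are two to three times the stated one. Still, 7% is a weak bound: it is reported as a result while recruitment is described in the future tense.
- **The completer set or the imputation may leave GEE with few or no incomplete records.** This is correct, and completer selection may then be the larger missing-data risk. It does not rescue the sentence. It means that the sentence has no function beside the other two rules.

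**Conclusion.** The statement is wrong as written: ordinary unweighted GEE is not generally valid under MAR. The practical consequence is conditional. Bias in the arm comparison needs score-dependent dropout that differs by arm, together with a working correlation that is not correct. At the stated 7% loss it reaches about 0.15 SD at worst, less than half a standard error, and it becomes material only if attrition is well above that. These sizes rest on the assumed SD, correlations and dropout slope.

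The documents do not support reading this as a demonstrated bias in the trial's result. Severity is moderate: this is a 40-patient safety and feasibility trial whose Outcomes section ranks the cognitive scales as secondary.

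**What to change.** - For the scales treated as continuous, replace the GEE sentence with a mixed model for repeated measures: REML, arm by visit, baseline score, unstructured covariance and Satterthwaite degrees of freedom. Fit it to all randomised patients with any post-baseline score. This model is valid under MAR when correctly specified.
- If GEE is kept, make it inverse-probability-weighted and say so.
- Reconcile the section. State which analysis set this model uses, given the completer per-protocol rule, and whether the single random forest imputation feeds it, supplements it or is dropped. As written, one sentence imputes the cognitive scores, another says that no imputation is needed, and a third keeps only completers.
- A delta-shift sensitivity analysis for data missing not at random is an optional extra, not part of this correction.

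The cost is small: a changed analysis population for this model, slightly more analysis work, and a different procedure in the SPSS software already named. No new data are needed.

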To evaluate the long-term efficacy of RIC, the study includes a 12-month follow-up period with assessments at 6 and 12 months. These evaluations include neurocognitive scales and blood biomarkers analyses. The RIC intervention itself is administered over a 3-month period, with data collection points at baseline, 3 months, 6 months, and 12 months to systematically assess its sustained effects (Figure 2).

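### GEE is put forward as suited to a small sample, but with 20 participants per arm its usual robust-variance Wald test would run above 5%: about 6.4% for a single visit contrast and about 9% for a 3-df group-by-visit test

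*Protocol article*

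**What the plan says.** The second paragraph of Statistical analysis in the Protocol article opens by saying "we implemented two strategies appropriate for small-sample longitudinal data". The first strategy is a single random forest imputation. The second is GEE: "Generalized Estimating Equations (GEE) will be used to model outcome trajectories", assuming data are missing at random.

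The other relevant statements are:

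- Size: "A total of 40 participants will be randomly assigned" (Study design), and "this project targets 20 patients in each group" (Sample size estimation).
- Visits: "with data collection points at baseline, 3 months, 6 months, and 12 months" (Interventions).
- Test level: "with a significance level of *p* < 0.05" (Statistical analysis).
- Software: "Statistical analysis will be performed using SPSS version 20" (Statistical analysis).

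The article does not name the GEE variance estimator, the test statistic, the reference distribution, the working correlation or the coding of time.

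Outcomes for efficacy lists the cognitive and functional scales and the biomarkers as secondary. The Abstract calls the four clinical scales primary efficacy endpoints. Outcomes for safety makes safety primary.

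**The concern.** The text offers GEE as an answer to the small sample. For routine GEE inference the logic runs the other way. The robust (sandwich) variance is justified as the number of independent clusters grows. With few clusters it is biased low, and a normal or chi-square reference ignores the uncertainty in the variance itself. Here the clusters are participants, 20 per arm.

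If the routine version is run, the trajectory analyses of MMSE, MoCA, CDR, ADL and the biomarkers would be tested at more than the declared 5%, and their intervals would be somewhat too narrow. The excess grows with the degrees of freedom of the test. It therefore matters most for a joint test across visits, which is one natural reading of modelling trajectories over four unevenly spaced visits.

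**Working it through.** **Figure to compare with.** The plan states a 5% level. It gives no GEE calculation to reproduce, so the check asks what size a nominal 5% test would have.

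**Inputs from the article.** n = 20 per arm; four visits, so group-by-visit has 3 df when visit is categorical; nominal level 0.05; 7% loss of MoCA at 12 months.

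**Assumptions not in the article.** Uncorrected robust variance, Wald test, chi-square (or normal) reference, two-sided 1-df tests, normal errors.

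**Closed form.** With a mean for each arm and visit and complete data, the uncorrected sandwich equals the within-arm covariance with divisor n instead of n − 1. The Wald statistic is then Hotelling's T² × n/(n − 1), with 2n − 2 = 38 df. For a p-df test:

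size = P( F(p, 39 − p) > χ²₀.₉₅(p) × (19/20) × (39 − p)/(38p) )

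- p = 1: 3.841 × 0.95 × 38/38 = 3.649; P(F(1,38) > 3.649) = 0.064.
- p = 3: 7.815 × 0.95 × 36/114 = 2.344; P(F(3,36) > 2.344) = 0.089.
- p = 3 with 18 per arm, to allow for loss: 0.094.
- p = 3 with 50 and 100 per arm: 0.064 and 0.057. The excess is a small-sample effect.

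In this setting the size does not depend on the within-patient correlation.

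**Intervals.** Width relative to the t-based interval: 1.96 × √(19/20) / 2.024 = 1.910/2.024 = 0.944, so about 6% too narrow. Coverage is 1 − 0.064 = 93.6%. Correcting it widens intervals by 1/0.944 = 1.06.

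**Simulation.** GEE with exchangeable working correlation, 20 per arm, 8,000 runs per setting (Monte Carlo SE about 0.3 points), true correlation exchangeable at 0.6 or decaying with time:

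| Setting | 3-df group-by-visit, robust Wald |
|---|---|
| Complete data | 9.0% |
| 7% dropout | 9.1% to 9.7% |
| 20% dropout | 9.3% to 9.5% |
| Skewed errors, complete data | 7.9% |

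A linear-time slope by group ran at 6.1% to 7.0%. A separate check with a standard GEE routine (1,500 runs, SE about 0.8 points) gave 9.8% for the 3-df test.

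**Other variants, 20 per arm, 3 df.**

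- Generalized score test, same robust variance, chi-square reference. It rejects when 40 × T²/(T² + 38) > 7.815, that is T² > 7.815 × 38/(40 − 7.815) = 9.227. Then F = 9.227 × 36/114 = 2.914, and P(F(3,36) > 2.914) = 0.047. The 1-df version gives 0.052.
- Model-based variance with the correct working correlation: 5.4% simulated.
- Corrected variance (divisor n − 1), still with chi-square: 7.815 × 36/114 = 2.468; P(F(3,36) > 2.468) = 0.078. A bias-reduced sandwich gave 7.5% in simulation.
- Corrected variance and F reference: 4.7% to 5.6% simulated with normal errors, at 0% to 20% dropout.

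The last two lines show that correcting the variance alone is not enough; the reference distribution must change too.

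**The case against.** The strongest objection is that the 9% needs a chain of choices the article does not make: uncorrected sandwich, Wald test, chi-square reference, categorical visit and a joint 3-df test. An article may leave such details to a fuller plan, and their absence is not a fault. This stands. A reader might infer that GEE at this sample size has a 9% error rate. The documents do not support that: the score test and a correctly specified model-based variance stay near 5%, and the article specifies no joint group-by-visit test.

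Two further inferences also fail. One is that every trajectory comparison is inflated to about 9%; single contrasts and linear slopes run at about 6% to 7% under the same assumptions. The other is that GEE p-values decide whether a Phase II trial follows; Sample size estimation ties that step to safety and feasibility.

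It can also be said that the small-sample phrase introduces a paragraph on missing data and says nothing about variance calibration. That is fair as to context. Even so, the sentence gives the small sample as the reason these methods suit the trial, and for routine GEE inference that reason is wrong. The point rests on this stated rationale, not on an omitted detail.

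**Conclusion.** The point holds in conditional form. The unqualified statement that GEE is appropriate for this small sample is not justified for GEE with its usual robust variance. Under the ordinary robust-variance Wald test with a chi-square reference, a nominal 5% test runs at about 6.4% for one visit contrast and about 9% for a 3-df group-by-visit test, and intervals are about 6% too narrow. That choice of test is an assumption, and normal errors are assumed too; one skewed-error check gave 7.9% for the 3-df test.

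The importance is moderate at most. The analyses affected are the efficacy and biomarker trajectories, which Outcomes for efficacy lists as secondary even though the Abstract gives the clinical scales a higher label. The primary safety outcome is untouched.

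**What to change.** In Statistical analysis, choose one of the following and state it:

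- GEE with a bias-corrected (small-sample) sandwich variance **and** a t or F reference distribution. Both parts are needed.
- A small-sample-valid alternative, such as a likelihood-based repeated-measures model with Kenward-Roger or Satterthwaite degrees of freedom. Replacing GEE is an option, not a necessity.

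In either case, remove the unqualified statement that GEE is appropriate for small samples, or tie it to the correction chosen.

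The cost is a sentence or two and no new data. Intervals become about 6% wider, which is their proper width. There is slightly more analysis work, and the correction may lie outside the routine options of the stated software, so this should be checked before the text is fixed.
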